**Methods/design:**

In order to compare pharmacological treatment (paroxetine) and psychological treatment (TF-CBT) in (cost-) effectiveness on the short and the long term, we will randomize 90 patients with chronic PTSD to either paroxetine (24 weeks) or TF-CBT (10–12 weeks). We will assess symptom severity and costs before and after the intervention with the Clinician Administered PTSD Scale (CAPS), the Clinical Global Impression Scale (CGI) and the Trimbos/iMTA questionnaire for Costs associated with Psychiatric Illness (TiC-P).

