### Study design

The study is designed as a randomized controlled trial comparing TF-CBT and paroxetine treatment. The randomization and allocation procedure will be performed by a researcher who has no further role in data collection. The study design was set up with one pre-treatment assessment and four post-treatment assessments (at 1 week, 6 months, 12 months and 18 months) but before starting data-collection the authors added an assessment at 3 months as well (see Figure 1). All assessments will be performed by research workers blinded for the allocated treatment. The study will be performed at the department of psychiatry of the Academic Medical Center (AMC) in Amsterdam. Patients will be recruited over the course of 3 years, starting November 2009.

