### Sample Size

#### Sample size calculation

To compare the effectiveness of both interventions, the difference in CAPS scores between the two groups will be analyzed. We expect differences in effectiveness and cost-effectiveness between both treatments to be most prominent at follow-up, i.e. 6 months, 12 and 18 months after cessation of the 12-week treatment periods and therefore sample size calculations should ideally be based on expected differences at follow-up. However, due to very few data available for long-term power calculations, we initially choose to be conservative in our sample size calculation. Based on an earlier RCT on the efficacy of CBT and another RCT on the efficacy of paroxetine in the treatment of PTSD, we expect to find a total CAPS score of 23.7 (SD=26.1) in the cognitive behavioral group [38] and of 34.8 points (SD=25.7) in the paroxetine group [15]. Power calculations showed that a total of 89 participants in each treatment group will be required to demonstrate a difference of 11.1 points (alpha=5%, power=80%). To allow for 20% attrition at follow-up, we will assess 234 patients (N=117 in each treatment group).

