#### Sample size calculation adjustment

We decided to adjust the sample size calculation and to optimize the power of the trial given the current study design, resulting in a smaller but more feasible sample size, in the light of possible slow recruitment. The original sample size calculation was based on the outcome on a single follow-up measurement, and was therefore rather conservative. As repeated measurements during follow-up provide additional data, differences can be estimated with higher accuracy, and therefore a smaller sample size is required to demonstrate a similar difference.

The increase in power does not solely depend on the number of measurements, but also on the correlation between measurements on the same patient (intra class correlation or ICC). Additional measurements add relatively less information to previous measurements if measurements are highly correlated. The required sample size for our study was therefore based on the study of Rochon [39] showing that for five measurements on each patient, for ICCs from 0 to 0.5, between 36 and 68 patients are required in each arm with an effect size of Cohen’s *d*=0.3, while between 14 and 25 patients per arm are needed with an effect size of 0.5. With an anticipated effect size of 0.46 we would need between 20 and 36 (depending on the actual ICC) patients per measurement per arm, respectively to gain a difference of 12 points on the CAPS at 18 months post-treatment. Anticipating possible attrition of study participants of 20%, we aim for 45 patients in each arm for the entire study period. Our new sample size is in line with another comparative study on long-term treatment effects of SSRI versus trauma-focused psychological treatment up to date that indicates that a smaller sample size may be sufficient to demonstrate a difference at 6-month follow-up [11].

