### Economic evaluation

The economic evaluation will be performed from a societal perspective, with the costs per unit improvement on the primary outcome (CAPS score) as the primary outcome measure. The appropriate type of economic evaluation is conditional on the results [65]. We hypothesize that a more effective intervention will be associated with less health care utilization as well as less burden to relatives (time costs) and absence from paid work (productivity costs). Therefore, the primary analysis in the economic evaluation will be a cost-effectiveness analysis that evaluates costs associated with an improved PTSD outcome in terms of CAPS scores. In addition, a secondary analysis will evaluate cost differences in relation to differences in quality-adjusted life years (QALYs). This cost-utility analysis, resulting in an incremental cost-effectiveness ratio expressed in costs per QALY, will be included to allow comparison with other health-related interventions or programs. With a study horizon of 18 months, no discounting will be applied.

We will differentiate between direct medical, direct non-medical and indirect costs. Direct medical costs are associated with health care utilization related to the pharmacological or psychological treatment, as well as to inpatient and outpatient mental health care, day-treatment and primary physician care. Direct non-medical costs are generated by travel to and from health care providers. Indirect costs are associated with lost productivity due to absence from paid work.

Health state utilities to estimate QALYs will be derived from an EQ-6D measurement at baseline, as well as the follow-up assessments. Utility values for EQ-6D scores will be based on UK-estimates [53]. Utility scores will be uniformly interpolated, assuming constant health state between subsequent assessments.

Robustness of the results for uncertainty in the assumptions will be evaluated in sensitivity analyses, including: Dutch health states [66] and a linear interpolation between EQ-6D measurements, varying unit costs for pertinent volumes of health care utilization (e.g. therapy costs, productivity costs). In model-based analyses using data from literature about these middle to long-term effects and costs associated with PTSD patients we will extrapolate the results to estimate the effectiveness and cost-effectiveness for both treatment options on long term (3–5 years).

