### Strengths and limitations

A particular strength of the study is that it is unique in comparing a pharmacological treatment with psychological treatments on the short and the long term. Its sample size is sufficient to differentiate the treatment in effectiveness and cost-effectiveness over the short and the long term, where at present only studies are available that did not take into account long-term effects [11,28].

Some limitations may affect the trial that need to be considered. Firstly, even though we aimed to reduce different influencing factors between pharmacological factors and psychological factors, this is rather difficult as the nature of the two treatments differs. Regarding this difference, the two treatments vary in duration as well as in number and length of the sessions, with pharmacological treatment approximately 24 weeks and psychological treatment consisting of approximately 12 weekly sessions. As we already outlined previously, the length of pharmacological treatment is very essential with possible high relapse rates during short-term treatments [29,31]. Despite these differences, we strived for similarity within the protocols as much as possible; both protocols consist of comparable psycho-education as well as a relapse prevention session. Furthermore, questionnaires will be performed in the same order in both treatment protocols. Other differences intertwined in the nature of both treatments should not be eliminated since the comparison of both treatments should be based on conditions that reflect routine clinical practice in this pragmatic effectiveness trial.

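### The 18-month horizon that justifies no discounting is counted from the end of treatment, while costs and utilities start at baseline: about 20 to 24 months, and about 3 months longer for paroxetine

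*Protocol article*

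**What the plan says.** All references are to the protocol article.

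- **Discounting.** Economic evaluation: "With a study horizon of 18 months, no discounting will be applied". No other discounting rule appears.
- **Start of accrual.** The same section includes the cost of the two study treatments among direct medical costs, and utilities are "derived from an EQ-6D measurement at baseline, as well as the follow-up assessments".
- **Timing of the 18-month visit.** Study design lists "four post-treatment assessments (at 1 week, 6 months, 12 months and 18 months". The sample size adjustment aims "to gain a difference of 12 points on the CAPS at 18 months post-treatment". The first sample size calculation speaks of follow-up "6 months, 12 and 18 months after cessation of the 12-week treatment periods".
- **Treatment duration.** The abstract has "either paroxetine (24 weeks) or TF-CBT (10–12 weeks", and Strengths and limitations has "pharmacological treatment approximately 24 weeks and psychological treatment consisting of approximately 12 weekly sessions".
- **Longer horizon.** At its end, Economic evaluation plans model-based analyses to "extrapolate the results to estimate the effectiveness and cost-effectiveness for both treatment options on long term (3–5 years".

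**The concern.** The decision not to discount rests on one number, and that number does not describe the period over which costs and QALYs are collected. Eighteen months is the distance from the end of treatment to the last visit. The economic totals start earlier, at baseline, and the treatment phase differs in length between the arms.

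Two things follow. The stated reason for not discounting understates the horizon. More directly, if totals are summed from baseline to each patient's last visit, the paroxetine arm collects costs and QALYs over a longer calendar period than the TF-CBT arm. Differences in cost and in QALYs would then partly reflect unequal observation time. An 18-month rationale also says nothing about a 3 to 5 year model.

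**Working it through.** **1. The plan's own figure.** Eighteen months reproduces only as the time from the end of treatment to T5. It does not reproduce as the time from baseline to T5.

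**2. Horizon from baseline.** Formula: treatment weeks × 7/30.4375 + 18 months. Treatment is assumed to start at baseline; any wait would lengthen the period.

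| Arm | Weeks | Treatment (months) | Baseline to T5 (months) |
|---|---|---|---|
| TF-CBT | 10 | 2.30 | 20.3 |
| TF-CBT | 12 | 2.76 | 20.8 |
| Paroxetine | 24 | 5.52 | 23.5 |

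The arms differ by 23.52 − 20.76 = 2.8 months to 23.52 − 20.30 = 3.2 months. As a share of the TF-CBT period this is 2.76/20.76 = 13% to 3.22/20.30 = 16%. If follow-up were counted from the end of a taper from the maximum dose (3 to 6 weeks at the weekly decrements given), the paroxetine period would be 24.2 to 24.9 months.

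The first sample size calculation refers to 12-week treatment periods without distinguishing the arms. This conflicts with the 24 weeks given elsewhere for paroxetine, and the passages must be reconciled. On that reading both arms run 20.8 months: the arm difference disappears, but the mismatch with 18 months remains.

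**3. Size of not discounting.** The article gives no rate, so annual rates r of 1.5% and 4% are assumed, with year 1 undiscounted. For a level stream over T years, the overstatement is T divided by the discounted length, minus 1. For T between 1 and 2 years the discounted length is 1 + (T − 1)/(1 + r). For whole years it is the sum of (1 + r)^−(k−1) over k = 1 to T.

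Example: T = 1.96 years (23.5 months), r = 4%: 1 + 0.96/1.04 = 1.923, and 1.96/1.923 − 1 = 1.9%.

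| Period | r = 1.5% | r = 4% |
|---|---|---|
| 18 months, as stated | 0.5% | 1.3% |
| 20.8 months | 0.6% | 1.7% |
| 23.5 months | 0.7% | 1.9% |
| 3 years | 1.5% | 3.9% |
| 5 years | 3.0% | 8.0% |

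The last two rows apply only if the model is left undiscounted. Correcting the horizon from 18 months to its actual length adds about 0.1 to 0.6 percentage points. If discounting ran continuously from day 1, the trial-period figures would be 1.3% to 3.9% and the 5-year figures 3.8% to 10.1%, still modest within the trial.

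**The case against.** The strongest reply is that this is loose wording with little numerical effect. Not discounting over less than two years is a disclosed choice, and discounting after month 12 is a convention from outside the article. The primary economic measure is cost per unit of CAPS improvement, and a score difference is not a stream, so the arithmetic above applies only to costs and to the secondary QALY analysis. All of this stands, and it limits the discounting part of the point. It does not answer the mismatch in the stated horizon or the unequal accrual period.

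Two stronger readings are tempting, and the article supports neither.

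- A reader might infer that the 3 to 5 year model will be undiscounted. The article does not say so. Its no-discounting sentence is tied to 18 months and follows the trial-based analyses. The model is introduced later as a separate exercise, and a condensed article may leave its discounting rule to the full plan. What can be said is that the 18-month reason does not carry over.
- A reader might infer a bias in favour of TF-CBT. Research aims and hypotheses does expect the TF-CBT advantage mainly at long-term follow-up. If that held, undiscounted late gains and late avoided costs would both favour TF-CBT. But it is a hypothesis, both treatments' planned costs fall within the first year, and no cost-effectiveness ratio can be computed from the article. The direction is conditional, not shown.

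**Conclusion.** The point holds in limited form. The single ground for not discounting, an 18-month horizon, is inconsistent with a schedule timed from the end of treatment and with accrual from baseline. The period is about 20.3 to 20.8 months for TF-CBT and 23.5 months for paroxetine, taking the arm-specific durations in the abstract and in Strengths and limitations.

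The effect of not discounting within the trial is small, about 1% to 2% of a level stream at assumed rates of 1.5% to 4% with year 1 undiscounted. The accrual difference of about 3 months between arms matters more: a level stream summed to each arm's last visit would be 13% to 16% longer under paroxetine for that reason alone. This presumes that totals run from baseline to T5; the article does not say that they are cut at a common date.

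**What to change.** In Economic evaluation:

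1. Define one economic horizon counted from randomisation, the same for both arms. Restate the 18-month figure with its starting point, and count costs and QALYs only within that horizon. On the planned schedule both arms are observed to at least about 20 months from baseline. A horizon of 18 months from randomisation would therefore be covered. It falls about 15.2 to 15.7 months after TF-CBT ends (18 − 2.76 and 18 − 2.30) and 12.5 months after paroxetine ends (18 − 5.52), between T4 and T5 in both arms. The planned interpolation then gives the QALYs, and costs in that last interval need apportioning.
2. Discount costs and QALYs that accrue after month 12 at a stated annual rate, and show the undiscounted result as a sensitivity analysis.
3. State separately whether and at what rate the 3 to 5 year model discounts costs and effects.
4. Reconcile the 12-week treatment periods in the sample size calculation with the durations given elsewhere.

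The cost is wording and trivial computation. No visit, instrument or sample size changes.

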## Discussion

This RCT represents a unique study that aims to directly compare the most commonly used psychological intervention (TF-CBT) and pharmacological intervention (paroxetine) on (cost-) effectiveness in PTSD patients on the short and the long term. Although there is ample evidence that both treatments are effective, a systematic head to head comparison on the short term and especially on the long term is lacking. Thus far, only a handful of studies have compared pharmacological and psychological treatments directly [11,28] and there is uncertainty on the comparative longer term effectiveness and cost-effectiveness of these treatments.

Gaining insight in effectiveness of treatment in terms of reduction of PTSD symptoms will reduce significant personal suffering and help to reduce societal costs (i.e. regain of productivity and reduce sick leave) not only during treatment but also on the long term.

### Strengths and limitations

A particular strength of the study is that it is unique in comparing a pharmacological treatment with psychological treatments on the short and the long term. Its sample size is sufficient to differentiate the treatment in effectiveness and cost-effectiveness over the short and the long term, where at present only studies are available that did not take into account long-term effects [11,28].

Some limitations may affect the trial that need to be considered. Firstly, even though we aimed to reduce different influencing factors between pharmacological factors and psychological factors, this is rather difficult as the nature of the two treatments differs. Regarding this difference, the two treatments vary in duration as well as in number and length of the sessions, with pharmacological treatment approximately 24 weeks and psychological treatment consisting of approximately 12 weekly sessions. As we already outlined previously, the length of pharmacological treatment is very essential with possible high relapse rates during short-term treatments [29,31]. Despite these differences, we strived for similarity within the protocols as much as possible; both protocols consist of comparable psycho-education as well as a relapse prevention session. Furthermore, questionnaires will be performed in the same order in both treatment protocols. Other differences intertwined in the nature of both treatments should not be eliminated since the comparison of both treatments should be based on conditions that reflect routine clinical practice in this pragmatic effectiveness trial.

Another possible limitation may lie in the fact that we only include PTSD patients that are able to receive monotherapy with either TF-CBT or paroxetine. Some patients may not be eligible for exposure or monotherapy with pharmacotherapy due to a variety of reasons, such as the presence of primary severe depressive disorder or suicidal ideation, other comorbid disorders (i.e. personality disorders) and severe psychosocial problems that may interfere with treatment. Patients with more severe PTSD symptoms are often recommended combination therapy with both pharmacotherapy and psychotherapy [33]. A recent meta-analysis [67] comparing the effectiveness of combination therapies with the separately delivered interventions, could however not draw clear conclusions due to lack of evidence and urged for large randomized controlled trials. Despite the fact that combination therapies are common, and direct comparison leads to exclusion of patients with more complex symptoms, we nonetheless think it is very important to first carefully investigate the relative superiority of one treatment to another. By directly comparing these separate treatments we will be able to draw solid conclusions on (cost-) effectiveness.

### Implications for practice

Clinicians’ decisions about optimal care, and the clinical practice guidelines that inform these decisions, will of course rely to a large extent on evidence from adequate RCTs. For example, recently, a growing number of studies on the effectiveness of Eye Movement Desensitization and Reprocessing (EMDR) have been conducted (i.e. [10]) as well as meta-analyses (i.e. [34]) and reviews (i.e. [68]), comparing results across RCTs on EMDR and other treatments, showing that EMDR is equally effective as TF-CBT (see also Nijdam et al. [12]). This finding led to recommendation and implementation of EMDR as a first-line psychological treatment besides TF-CBT. Likewise, evidence on the direct comparison of effective psychological and pharmacological interventions regarding (cost-) effectiveness is scarce and this RCT may help answering questions concerning the most optimal care. If our premise that TF-CBT is superior to paroxetine in terms of sustainable effectiveness and cost-effectiveness for the treatment of PTSD, this could have major implications for current clinical practice.
